# Protocol for a feasibility randomised controlled study of a multicomponent intervention to promote a sustainable return to work of workers on long-term sick leave — PROWORK: PROmoting a Sustainable and Healthy Return to WORK

**DOI:** 10.1186/s40814-022-01143-8

**Published:** 2022-08-19

**Keywords:** Return to work, Long-term sickness absence, Mental health, Small and medium enterprises, Large enterprises, Positive communication, Worker, Manager, Intervention

## Abstract

**Background:**

The cost of sickness absence has major social, psychological and financial implications for individuals and organisations. Return-to-work (RTW) interventions that support good quality communication and contact with the workplace can reduce the length of sickness absence by between 15 and 30 days. However, initiatives promoting a sustainable return to work for workers with poor mental health on long-term sickness absence across small, medium and large enterprises (SMEs and LEs) are limited. This paper describes the protocol of a pilot randomised controlled trial (RCT) to test the feasibility of implementing a RTW intervention across SMEs and LEs across all sectors.

**Methods and design:**

A two-arm feasibility RCT with a 4-month intervention will be conducted in SMEs and LE enterprises from the Midlands region, UK. At least 8 organisations (4 controls and interventions), and at least 60 workers and/or managers, will be recruited and randomised into the intervention and control group (30 interventions, 30 controls). Workers on long-term sickness absence (LTSA) (between 8 and 50 days) and managers with a worker on LTSA will be eligible to participate. The intervention is a behavioural change programme, including a managers and workers RTW toolkit, focused on supporting sickness absence and RTW through the provision of knowledge, problem-solving, action planning, goal setting and positive communication that leads to a sustainable RTW. Organisations assigned to the control group will continue with their usual practice. Measurements of mental health, RTW, work outcomes, quality-of-life, workplace support and communication and other demographic data will be taken at baseline, 2 months and 4 months. Feasibility will be assessed based on recruitment, retention, attrition, completion of measures and intervention compliance for which specific process and research outcomes have been established. A process evaluation will explore the experiences and acceptability of the intervention components and evaluation measures. Exploratory economic evaluation will be conducted to further inform a definitive trial.

**Discussion:**

This is a novel intervention using a worker-manager approach to promote a sustainable return to work of workers on long-term sick leave due to poor mental wellbeing. If this intervention is shown to be feasible, the outcomes will inform a larger scale randomised control trial.

**Trial registration:**

ISRCTN90032009 (retrospectively registered, date registered 15th December 2020)

## Background

In Britain, mental health issues increasingly account for a significant proportion of long-term sickness absence from work [1], and those who are absent for 6 months or longer have less than a 50% chance of ever returning to employment [2]. Sickness absence associated with poor mental health costs UK employers £7 billion each year [1], and a recent report by the Office for National Statistics (2019) [3] suggests sickness absence due to poor mental health is on the rise (12.4% in 2018 compared to 9.1% in 2009). The cost of sickness absence is not at an economic level only, as there are major social, psychological and financial implications for individuals on sick leave and for those unable to RTW [4]. These include inactivity, isolation, reduced workability and productivity [5–8], with reduced wellbeing and impaired self-image leading to the individual potentially withdrawing from society and support networks [5]. Long-sickness absence is also a predictor of disability pension, higher risk of unemployment and job termination [9]. Therefore, early intervention to support a worker’s RTW is not only cost-effective for the employer (e.g. in terms of reduced turnover, recruitment costs, retention of knowledge) but also is vital for workers’ health and wellbeing.

A systematic review and meta-analysis of randomised controlled trials (RCT) and cluster RCTs published by Nigatu and colleagues (2016) [10] found that RTW interventions providing regular contact and communication with the individual’s workplace alongside health interventions based on cognitive behavioural therapy or a problem-solving approach were effective in reducing the number of sick leave days (−13.38 days) in individuals with a common health problem. These findings are supported by a more recent systematic review and meta-analysis led by Mikkelsen (2018) [11], who observed an average reduction in time until RTW of 15–30 days, and by Nieuwenhuijsen and colleagues (2020) [12] who reported in their Cochrane review that a combination of work-directed and clinical interventions (such as psychological treatment) reduces sickness absence days within the first year of follow-up (*SMD* −0.25, 95% *CI* −0.38 to −0.12: 9 studies). These studies support the economic value of investing in evidence-based RTW interventions. However, in the UK, the RTW of workers on long-term sick leave is usually managed by employers with the responsibility given to line managers, particularly in small- and medium-sized organisations. In some cases, employers may outsource the RTW support to external occupational health providers. Recommendations from the National Institute for Health and Care Excellence (NICE) (2019) [13] indicate that organisations should develop policies and procedures that promote health and wellbeing and a sustainable RTW. Yet, information regarding specific actions of how to achieve it is limited. The NICE guidelines (2019) [13] further recommend for employers to make early and positive contact with their workers on long-term sick leave to make them feel supported, valued and confident about returning to work. Early communication may also prevent the development of poor mental health as a comorbidity in workers on long-term sickness due to other health conditions [14].

The outbreak of coronavirus SARS-2 (COVID-19), declared a pandemic by the World Health Organization (WHO) in March 2020, presents a challenging scenario for a safe RTW following long-term sick leave, particularly amongst those workers with poor mental health and wellbeing. Since early in 2020, drastic changes to workplaces have been implemented to ensure the safety of all their workers, which means that some workers will have to RTW remotely following a period of sick leave or may experience additional anxiety towards RTW on site. Small- and medium-sized enterprises (SMEs) may have limited resources to support these workers, and they are also less likely to have formal policies and procedures in place to keep in touch with people on sickness absence. Therefore, initiatives promoting a supportive and sustainable RTW experience for workers with poor mental health are now more important than ever and particularly amongst SMEs (with 10 to 249 workers). In the UK, these account for 99.9% of the business population (5.9 million businesses) [15].

Based on recent evidence and the NICE (2019) guidelines [13], this proposed pilot randomised controlled trial (RCT) will test the feasibility of implementing a RTW intervention for workers on long-term sickness absence due to poor mental wellbeing or with poor mental health as a comorbidity across SMEs and LEs across all sectors. This intervention has been named PROWORK (PROmoting a Sustainable and Healthy Return to WORK).

### Study aims and objectives

The primary aim of this study is to undertake a pilot RCT (PROWORK) to test the feasibility of implementing a RTW intervention across SMEs and large enterprises (LEs) from a range of sectors. Secondary aims include the evaluation of the primary research outcome to inform a fully powered definitive RTW trial and to conduct a full cost-utility analysis. The objectives of this pilot study are therefore as follows:

#### Objectives

Assess potential selection bias in control and intervention organisations as measured using participant characteristics at baseline.Estimate retention of participants in the research evaluation at each follow-up timepoint across both control and intervention groups.Assess implementation of intervention delivery, dose, fidelity engagement and adherence by workers and their line managers (or those with a responsibility for managing RTW).Assess likely changes in the primary outcome (number of days until RTW part-time or full time).To describe questionnaire data outcomes of interest (e.g. anxiety, depression; readiness to RTW)To provide an early estimate of the costs, both healthcare and societal costs, in both intervention and control groupsDetermine the willingness and readiness of employers and their workers to adopt the proposed intervention in a manualised format (written as an instruction manual) but that is flexible enough to meet individual and organisational needs in different settings.

## Methods/design

### Study design

This is a feasibility randomised controlled trial with a 4-month intervention (called PROWORK) to be delivered to employees and managers in SMEs and LEs. Each of the organisations are the units of randomisation (the clusters), with data collected from individual workers (the participants). In addition, managers with a worker on LTSA will be eligible to participate. Although dyads of managers and workers can participate, this is not essential. This design overcomes the problem of contamination between the intervention and control arms and the problems associated with individually consenting and randomising workers to a trial where the employers may be managing the sick leave of 2 or more workers. A repeated measures design will be adopted, whereby worker participants will complete outcome measures at baseline, 2 months and 4 months, and managers will complete outcome measures at baseline and 4 months. Each organisation’s involvement in the trial is for 12 months. Observations and end-of-study interviews with workers and managers and informal monthly meetings with the organisation’s human resources representative will be conducted throughout the intervention period as part of a full process evaluation. Figure 1 shows the study flow diagram, and Table 1 indicates the schedule of enrolment, intervention and outcome measures. The project has been granted ethical approval by the Loughborough University Ethical Advisory Committee (reference 2020-1889-2041). The trial was preregistered in the ISRCTN registry on 15th December 2020 (10.1186/ISRCTN90032009).

**Fig. 1 Fig1:**
[figure not shown]
Study flow diagram

**Table 1 Tab1:** Standard Protocol Items: Recommendations for Interventional Trials (SPIRIT) diagram illustrating the design and timescales of the pilot PROWORK RCT

TIMEPOINT	Enrolment	Allocation	Baseline (0 month)	2-month follow-up	End of intervention (4-month)	End of study
**ENROLMENT**						
Organisation recruitment	x					
Eligibility screen	x					
Organisation informed consent	x					
Allocation		x				
Manager informed consent			x			
Worker informed consent			x			
**INTERVENTION**						
Worker and manager RTW toolkit			X	X	X	
Worker coaching sessions			X	X		
Manager training webinar			X			
Control group - usual practice			X	X	X	
**ASSESSMENTS**						
Organisational sickness policy data	X					
Organisational sickness report data			X			
Feasibility outcomes (recruitment)			X			
Feasibility outcomes (retention, compliance)					X	X
Process evaluation	X		X	X	X	X
Intervention resource used						X
Economic evaluation	X		X	X	X	X
**Worker measures**						
Demographics			X			
Days of sick leave			X	X	X	
Mental health			X	X	X	
Quality of life			X	X	X	
Healthcare resource used			X	X	X	
Return to work measures			X	X	X	
Workplace support and communication			X	X	X	
Work outcomes			X	X	X	
Intention to use toolkit			X	X		
Manager RTW actions				X	X	X
Interviews						X
**Employer measures**						
Demographics			X			
Mental health management experience			X			
RTW management experience			X			
RTW support for worker					X	X
Interviews						X

#### Setting

PROWORK is part of the Mental Health and Productivity Pilot (MHPP; https://mhpp.me/), a larger research programme which has been funded by the Midlands Engine (CPU 2640) to develop cost-effective and sustainable research to support good mental health at work, reduce stigma and increase productivity in businesses within the nine areas of the Midlands region in the UK. This is the UK’s largest regional economy outside London (£246 bn a year), and it is home to a sixth (11 million) of the UK’s population, concentrating a mixture of organisations ranging from advanced technology to transport, research and manufacturing. Therefore, this study will take place in a wide range of organisational settings across the Midlands and will involve small (10 to 49 workers), medium (50 to 249 workers) and large (over 250 workers) enterprises.

#### Sample size

Recommendations for feasibility pilot RCT sample sizes were followed. Guidance for pilot clinical trials [16] recommends recruiting a minimum of 4 clusters per arm. Additionally, feasibility RCTs are recommended to recruit between 24 [17] and 50 [18] participants per arm, consistent with the median sample size found in pilot RCTs [19]. This is in line with the guidance from the National Institute for Health Research (NIHR), which indicates that a sample size of 30 is appropriate to answer the questions posed by a feasibility trial [20]. To match these recommendations, we aim to recruit at least 8 organisations of all sizes (small, medium, large) (4 controls and interventions) and 30 participants, including workers and managers, in the intervention group and the 30 in the control group. Participating organisations will be recruited over a 6-month period; the recruitment of workers and their managers will continue for 18 months.

#### Organisation recruitment and inclusion criteria

Small, medium and large organisations from across all sectors within the Midlands region, UK, will be invited to participate in PROWORK. Organisations will be recruited via webinars, phone calls, newsletters, emails and social media. The study will also be advertised through the Mental Health Productivity Pilot (MHPP) programme’s network, where organisations can fill out an expression of interest form. Organisations who express an interest in the study will be asked to provide data on the prevalence of their long-term sickness absence over the last 12 months along with a description of their RTW policy and procedure to cross-check for any overlaps or contradictions to PROWORK. Those organisations with conflicting policies that overlap PROWORK will not be eligible for the study. Eligible organisations are small, medium and large organisations with at least 2, 4 and 6 workers, respectively, on long-term sick leave over the past 12 months and with no contradictory or overlapping RTW polices.

Organisations will be asked to promote the study to potential participants (workers on long-term sick leave and their managers) through direct email and newsletters. To ensure the organisations’ compliance and timely recruitment of participants, monthly meetings will be arranged between the research team and the appointed organisation leads.

#### Participant recruitment, inclusion criteria and consent

Within participating organisations, workers (over 18 years of age) that go on sick leave for at least 8 days (or from issue of fit note) and up to 8 weeks (50 days) and/or the person managing their sickness absence are eligible to participate. Sickness absence must be associated with either poor mental wellbeing or where poor mental wellbeing may be a comorbidity [14]. Once the worker on long-term sick leave is identified by the organisation, both the worker, and their manager, will be sent a detailed information sheet about the study so that they can make an informed decision about their participation. Those interested in taking part will contact the research team directly either by phone or email, at which stage they will be consented by the research team.

Workers on long-term sick leave will not be eligible to participate in PROWORK if they are on sick leave (a) with a psychotic episode such as schizophrenia, or with substance abuse, (b) whilst under formal investigation for misconduct or in the formal process of disciplinary action, (c) due to cancer and signed off work for at least 6 months and (d) due to a neurological condition (e.g. multiple sclerosis, Parkinson, dementia).

#### Allocation to intervention

In this pilot RCT, organisations will be stratified by size. To avoid study contamination, organisations will be randomised into the intervention or active control group after baseline measures are taken using an allocation ratio of 1:1. Randomisation will be carried out by computer-generated randomisation stratified by organisational size (small, medium or large).

Consented workers will be allocated to either the intervention or active control group based on the randomisation of their participating organisation. Baseline data will be collected from each participant prior to either being given the RTW toolkit (intervention group participant) or supporting information (active control group participant). The participating workers and employers will not be blinded in group allocation.

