### Employers

Employers will have access to a RTW training video at the start of the intervention study, prior to recruiting workers on sick leave. The key workplace person (e.g. the line manager) responsible for managing a worker on sick leave will receive an employer version of the toolkit and provided with advice on when and how to use it with a worker. For those individuals who are managing more than one worker on long-term sick leave, they will receive an email from the researcher at the start of each worker on long-term sick leave, to remind them to use the toolkit (once they had done the webinar training).

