#### Trial process-related outcome

Organisational data collection pre-randomisation is as follows:Summary of long-term sickness absence data for the past 12 months (only total numbers and % by reasons)Organisation size and sectorCopies of sickness absence policy and frameworksCopies of the work policy and frameworksDetails on mental health training and support available for managers

Organisational data collection post-randomisation and the duration of the study are as follows:Number of workers on sick leave (≥ 8 days) and their reasonsNumber of workers that employers have contacted to take part in the studyNumber of workers consenting to take partNumber of workers using the toolkit (data collected at interviews and website use)Number of persons responsible for managing the sick leave and RTW of workers consenting to take partNumber of persons responsible for managing the sick leave and RTW of workers attending the trainingNumber of persons responsible for managing the sick leave and RTW of workers using the employer toolkit (data collected at interviews and website use)

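### Organisations are said to be randomised after baseline, but the rest of the protocol needs their arm set before workers are identified, which leaves worker selection open to differ by arm

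*Protocol article*

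**What the plan says.** The Allocation to intervention section says "organisations will be randomised into the intervention or active control group after baseline measures are taken using an allocation ratio of 1:1". It then says "Consented workers will be allocated to either the intervention or active control group based on the randomisation of their participating organisation", requires each participant's baseline data before the toolkit or control information is handed over, and adds "The participating workers and employers will not be blinded in group allocation".

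Other sections describe the sequence differently:

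- **Table 1 (SPIRIT diagram):** the allocation column comes before baseline, and manager and worker consent are marked under baseline.
- **Employers:** "Employers will have access to a RTW training video at the start of the intervention study, prior to recruiting workers on sick leave". The Active control group section rules out training for controls while the study runs.
- **Trial process-related outcome:** under "Organisational data collection post-randomisation and the duration of the study are as follows" it lists workers contacted, workers consenting, and managers consenting and attending training.
- **Table 3:** managers' consent and training attendance are marked only in the pre-randomisation column.
- **Sample size:** "the recruitment of workers and their managers will continue for 18 months".
- **Participant recruitment:** the information sheet goes out "Once the worker on long-term sick leave is identified by the organisation". Entry is allowed from 8 to 50 days of absence.
- **Follow-up:** the Workers section runs the 4 months from the worker's own baseline. The section on primary worker measures ends data collection 4 months after randomisation.

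**The concern.** Two things are at stake.

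The first is that the order of randomisation, recruitment and baseline, which is the backbone of a cluster trial, is stated in ways that cannot all be followed.

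The second follows from the order that most of the text implies. If the organisation knows its arm before it looks for eligible workers, its arm can influence whom it identifies and how early in the absence. Cluster randomisation balances organisations in expectation; it does not balance workers picked after allocation is known. The entry window is wide, so a difference in timing could shift days absent at entry. It would then shift any outcome counted from the first day of absence.

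This bears on objective 1 (selection bias), on the objective of gauging likely change in days to return to work, and on the mean and SD that the pilot is meant to supply for the main trial.

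**Working it through.** **1. Can worker baseline precede randomisation of the organisation?** Each organisation takes part for 12 months and each worker is followed for 4. If follow-up must fit inside that period, workers can enter over 12 − 4 = 8 months. If entry runs throughout, the window is 12 months, which agrees with 6 months of organisation recruitment + 12 = 18 months of worker recruitment. If randomisation waited for all worker baselines, the first entrant could wait about 8 to 12 months, longer than the 4-month intervention. So the sentence cannot hold for individual worker baselines.

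**2. What do the other sections require?** Training is offered before workers are recruited and is denied to controls, so the arm must be known by then. Table 1 and the post-randomisation list give the same order. Table 3 disagrees on managers' consent and training attendance.

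**3. Which follow-up clock?** A worker entering k months after the organisation is randomised would have 4 − k months of data under the post-randomisation rule: 4 at k = 0, 2 at k = 2, none from k = 4. Under the worker-baseline rule every entrant has 4 months. With rolling entry the two rules cannot both apply.

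**4. How would selection reach the outcome?** Let A be days absent at entry and R the days from entry to return. Counted from absence onset, total days T = A + R. With no treatment effect,

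E(T, intervention) − E(T, control) = [difference in mean A] + [difference in mean R].

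If R does not depend on A, the second term is zero and the bias equals the difference in mean days absent at entry. Counted from worker baseline, the first term drops out. What remains is any dependence of R on A, which adjustment for A addresses. The protocol describes the outcome as days until, or taken to, return and fixes no start date. It gives no figure for A by arm, so the bias has no documented size.

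**5. Would the planned baseline comparison reveal it?** From the protocol: 4 organisations and 30 participants per arm, workers and managers together. My assumptions: two-sided 5%, normal approximation, ICC 0 to 0.10, and either all 30 or only 15 per arm being workers.

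Design effect = 1 + (m − 1) × ICC, with m = n/4; effective n = n / design effect; difference detectable with 80% power = √(2 / effective n) × (1.96 + 0.84).

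| Workers per arm | ICC | Design effect | Effective n | Power for 0.5 SD | Detectable at 80% power |
|---|---|---|---|---|---|
| 30 | 0 | 1.00 | 30.0 | 49% | 0.72 SD |
| 30 | 0.10 | 1 + 6.5 × 0.10 = 1.65 | 18.2 | 33% | 0.93 SD |
| 15 | 0 | 1.00 | 15.0 | 28% | 1.02 SD |
| 15 | 0.10 | 1 + 2.75 × 0.10 = 1.275 | 11.8 | 23% | 1.16 SD |

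To put this in days, suppose (an assumption) that entry is spread evenly over days 8 to 50. The SD is then 42/√12 = 12.1 days, and the detectable gap runs from 0.72 × 12.1 ≈ 9 days to 1.16 × 12.1 ≈ 14 days.

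**The case against.** **The phrase may mean organisation-level baseline only.** The protocol does collect absence and policy data before randomisation, and it treats participant baseline separately. On that reading the timing conflict in the allocation sentence goes away. This stands as a possible reading, but it confirms that workers are identified after open allocation, and it leaves the Table 3 and follow-up conflicts untouched.

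**The risk is already recognised.** Selection bias is objective 1, recruitment rates and baseline characteristics are compared by arm, and the baseline table includes days on sick leave. This stands and lowers the severity. But inspecting imbalance afterwards is not preventing it, and the comparison is weak at this size.

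**It is a feasibility trial.** The analysis is mainly descriptive, p-values are played down, and the progression thresholds concern referral and participation. This also stands: no efficacy decision hangs on the bias. The pilot's estimates nevertheless feed the main trial.

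**Stronger readings that the documents do not support:**

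- A reader might assume, say, entry on days 8–22 in one arm and 22–50 in the other and infer a spurious benefit like the cited 15–30 days. Those windows have midpoints 15 and 36, so the 21-day gap is built in, and no section supports them.
- A reader might infer that intervention managers are trained to make early contact and choose workers at their discretion. The webinar is described as covering conversations about mental health, the organisation does the identifying, and the research team takes consent.
- A reader might infer that baseline scores for manager actions are contaminated by training. Table 1 schedules that measure only from 2 months (Table 3 differs), employers are given access to the training with no statement that it is completed first, and no covariate use is planned.
- Lack of blinding does not show that workers know their arm when they consent; the protocol does not say when they learn it.

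**Conclusion.** The concern holds in a limited form. The stated time of randomisation does not fit Table 1, the training sequence or the list of post-randomisation data, unless baseline is read as organisation-level only. Table 3 and the two follow-up clocks need reconciling on any reading.

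Under the order that the text as a whole implies, unblinded organisations identify workers after allocation, so both who enters and how early may differ by arm. If days are counted from absence onset, the bias is about the between-arm difference in mean days absent at entry, provided that remaining absence does not depend on time already absent. The documents do not allow a figure for it.

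The planned check would often miss a moderate imbalance: power for 0.5 SD is 23% to 49% over the assumed ICC and worker numbers. The recruitment target is a minimum, so a larger sample would do better. The normal approximation is, if anything, generous with only eight clusters.

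For a feasibility study this is a moderate point. It should be corrected because the pilot is meant to assess selection bias and to inform the main trial, and a later analysis plan cannot change how workers were recruited.

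**What to change.** 1. State one order: organisation-level data, then randomisation of the organisation, then worker identification, consent and worker baseline. Bring the Allocation to intervention, Workers, Trial process-related outcome and primary worker measures sections, and Table 3, into line with it, including a single follow-up clock.
2. Send the same arm-neutral information sheet to all workers who meet the eligibility criteria.
3. Have each worker complete baseline before the arm is disclosed.
4. Count days to return to work from worker baseline, adjusting for days absent at baseline, which is already collected.
5. Report by arm the proportion of eligible workers referred and the days absent at entry, as the selection-bias diagnostics for objective 1. The counts already planned of workers on leave (with reasons), contacted and consenting supply most of what is needed.

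Cost: protocol wording, one shared sheet and minor extra analysis; participants learn their arm slightly later. These steps reduce the risk but do not remove it, because organisations still know their arm when they identify workers.
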